### CGM Assessment

Glycemic control will be assessed by a CGM device (Dexcom G6 Pro; Dexcom) every 5 minutes, over the ~48-hour experimental sessions. Reporting of variables will follow the most recent international guidelines consensus for clinical trials [48] and will include (1) time in range: 70-180 mg/dL; (2) time in tight range: 70-140 mg/dL; (3) time below range: <70 mg/dL; (4) time in level 1 hypoglycemia: 54-69 mg/dL; (5) time in level 2 hypoglycemia: <54 mg/dL; (6) time above range: >180 mg/dL; (7) time in level 1 hyperglycemia: 181-250 mg/dL; and (8) time in level 2 hyperglycemia: >250 mg/dL. Data will be reported as a percentage of time per day and as estimated hours and minutes per day. We will also report (9) average glucose concentration and (10) area under the curve, (11) glucose management indicator (used to predict long-term glucose exposure); (12) glycemia risk index (summary of the quality of glycemia), (13) glucose coefficient of variation; and (14) mean SD glucose (both are measures of dynamic glucose variability). Variables will be reported for the entire 48-hour collection period, for the first and second 24-hour periods, and stratified over 4 different periods: morning (6 AM to 12 PM), afternoon (12 PM to 6 PM), evening (6 PM to 12 AM), and nocturnal (12 AM to 6 AM) [11]. Individual data will be analyzed only if the percentage of data obtained is >70% of the anticipated amount of data collected during the collection period [48].

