### Statistical Analysis

The sample size was calculated using data from relevant literature using similar individuals and glucose-assessing tools (CGM) [11,14,52,53]. Conservative parameters were inserted in the G*Power program (Heinrich-Heine-Universität Düsseldorf, version 3.1.9.6) for a repeated measure ANOVA within interaction: effect size of 0.2 (for 24-hour average glucose concentrations), probability of error type **α** of 0.05, power (probability of error type 1 β) of 0.95, correlation among repeated measurements of 0.7 [54], and nonsphericity correction of 0.5 [55,56]. With these parameters, 15 individuals are required (actual power of 0.96). Considering a typical dropout rate of 25% to 40%, we will initially recruit 25 participants.

A collaborator outside the research team will double-enter data coded for allocation into a computer in separate spreadsheets, allowing the researcher responsible for data analysis to assess the data without access to allocation information. Allocation will only be revealed after statistical analyses are run. In case of doubts about data entry (missing values or values outside the reference range), the researcher responsible for data analysis will contact the collaborator outside the research team responsible for double entry of the data to check accuracy. There will be no interim analysis.

To ensure confidentiality, all study-related information will be securely stored at the study site. All participant information will be kept in locked file cabinets in areas with access controlled by the principal investigator. All laboratory specimens, reports, data collection, process, and administrative forms will be identified by a coded ID number only to maintain participant confidentiality. Records containing names or other personal identifiers, such as locator forms and informed consent forms, will be stored separately from study records identified by code number. No personal information from participants will be released outside the study. Full access to the complete dataset will be restricted to members of the research team.

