The statistical analysis will follow the principles of intention-to-treat analysis [57]. Thus, data from participants will be assessed as randomized, regardless of whether they received the randomized treatment, meaning that even if they fail to follow the physical activity and diet instructions, or fail to complete the sessions as required, their data will be included in the analyses. Furthermore, we will also analyze the data “per protocol” [58], meaning that participants who deviate from instructions will be excluded from the final analyses. Differences in results stemming from intention-to-treat and per-protocol analyses will be discussed accordingly. The available variables will also be compared between participants who withdraw from the study and those who complete the study.

The effect of resistance exercise on glycemic control will be calculated as the absolute and percentage change between control and resistance exercise situations. Data will be expressed as mean and SD, with a 95% CI. For the analysis of data normality, we will perform the Shapiro-Wilk test. For normally distributed data, ANOVA will be used with 1 source of variation (experimental condition). If a significant main effect is observed, the post hoc Tukey test will be conducted. For nonnormal data, the Kruskal-Wallis test or Friedman test will be used as appropriate. The effect size will be calculated and interpreted as follows: <0.2=no effect, 0.2-0.49=low effect, 0.5-0.79=medium effect, and >0.8=large effect [59,60]. The significance level is set at 5%. The Prism program (version 10.1.1, GraphPad Software) will be used to generate graphs and analyze results. This trial will be reported following the CONSORT (Consolidated Standards of Reporting Trials) guidelines [61-63].

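### No outcome or time window is designated primary: 98 CGM variable-by-window cells share one 5% level, and the 24 hours behind the sizing variable are not defined

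*Protocol article*

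**What the plan says.** The CGM Assessment section numbers its variables up to "14) mean SD glucose (both are measures of dynamic glucose variability". It then gives the windows: "Variables will be reported for the entire 48-hour collection period, for the first and second 24-hour periods, and stratified over 4 different periods", the last being morning, afternoon, evening and nocturnal blocks. The Psychological Responses section adds six ratings: exertion after each set, feeling, enjoyment, self-efficacy, discomfort and session exertion.

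The Statistical Analysis section gives one scheme for all of these. For normally distributed data, "ANOVA will be used with 1 source of variation (experimental condition"); then "If a significant main effect is observed, the post hoc Tukey test will be conducted". Nonparametric tests replace this where normality fails, and "The significance level is set at 5" percent. Analysis follows intention-to-treat with a per-protocol analysis added, and "Differences in results stemming from intention-to-treat and per-protocol analyses will be discussed accordingly".

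The sample size paragraph uses an "effect size of 0.2 (for 24-hour average glucose concentrations"). Nowhere does the article call an outcome primary. The aim and the hypothesis speak of glycemic control, which is a construct and not one measured variable.

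**The concern.** The hypothesis is that effort does not affect glycemic control. With no variable, window and contrast named to decide it, the answer depends on which of many cells is put forward. One chance significant cell could be cited against the hypothesis, and many non-significant cells for it. Tukey protects the three pairwise comparisons inside one cell and does nothing across cells.

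The sizing variable does not settle the matter, because 24-hour average glucose can be computed over several different 24-hour spans. These differ greatly in how much post-exercise time they contain.

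**Working it through.** **The plan's own figures.** The article states no false-positive rate to reproduce. Its sizing result (15 participants, power 0.96) comes out at 0.956 for an interaction test if 3 groups and 48 measurements are assumed; the article states neither count. Whether that calculation fits the planned analysis is a separate matter. Here the sizing paragraph matters for the variable it names and for N = 15.

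**1. Number of cells (CGM Assessment).**
- Windows: 1 (48 h) + 2 (24-hour periods) + 4 (clock blocks) = 7.
- Cells: 14 × 7 = 98.

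**2. Where the 24-hour windows fall (Study Type and Design).** The sensor is fitted at about 5 PM on day 1, the session starts at 9:30 AM on day 2, and the sensor is removed between 5 and 6 PM on day 3. The article does not say when the first 24-hour period starts; counting from fitting is the assumption here.

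| Window | Clock time | Relation to the session |
|---|---|---|
| First 24 h | 5 PM day 1 to 5 PM day 2 | 16.5 h before session start, 7.5 h from it |
| Second 24 h | 5 PM day 2 to 5 PM day 3 | begins 7.5 h after session start |
| 24 h from session start | 9:30 AM day 2 to 9:30 AM day 3 | fully recorded, but not a listed window |

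The evening and nocturnal blocks each occur once before the session (day 1 into day 2) and once after it (day 2 into day 3). The article does not say whether the two are pooled.

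**3. Expected false positives if all 98 cells are tested.**
- No condition differs in any cell: 98 × 0.05 = 4.9 false omnibus rejections. Correlation does not change this mean.
- Exercise differs from control, but the two efforts do not: the relevant error is a false high-versus-low difference after Tukey. With three conditions, and assuming 15 completers in a repeated-measures analysis, the error df are (15 − 1)(3 − 1) = 28. The 5% studentized-range point is 3.499, equivalent to |t| = 3.499/√2 = 2.474, with a two-sided tail of 0.0197 per pair. Then 98 × 0.0197 ≈ 1.9. Requiring a significant omnibus test first can only lower this.

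**4. Chance of at least one false omnibus result (no condition differs).** If independent, 1 − 0.95^98 = 0.993. The cells are not independent: times below and above range are sums of their levels, area under the curve over a complete fixed window is the mean times a constant, and the 48-hour values combine the two 24-hour ones. A simulation of 98 equally correlated two-sided tests at 5% gives the following; the correlations are assumptions, since the article gives none between cells.

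| Correlation | Chance of at least one | Median count |
|---|---|---|
| 0 | 99% | 5 |
| 0.3 | 94% | 3 |
| 0.5 | 77% | 2 |
| 0.7 | 50% | 0 to 1 |
| 0.9 | about 23% | 0 |

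**The case against.** The strongest reply is that an implied primary exists: a trial sized on 24-hour average glucose presumably means to judge itself on it. That is fair as to the variable. It does not supply the window or the contrast, so a reader who accepts it still cannot identify the primary analysis.

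Three further points stand in part.
- **Testing is inferred.** The CGM section says the variables will be reported. That each cell is tested follows only from the analysis section exempting none, so the counts above are conditional.
- **Other documents may say more.** The registration dataset listed as Appendix 4 is not shown, so the absence is established for the article only. Detailed multiplicity rules for secondary outcomes may properly sit in an analysis plan.
- **Per protocol adds little.** Counting it as a second set gives 196 tests and 196 × 0.05 = 9.8. Those analyses largely reuse the same data and act as a sensitivity check, so they are not counted here.

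A reader might infer that about five false findings are to be expected, or that any conclusion could be picked. The documents support neither. The first needs every condition to be equal in every cell, whereas the Discussion expects exercise to improve glycemic control. Under correlation, five separate false findings is also not the typical result. The second overlooks a hypothesis stated in advance, a blinded analyst, intention-to-treat as the governing principle and Tukey within each cell. Blinding does not cover the choice of emphasis, however, because that choice can be made once allocation is revealed. Reading non-significance as proof of no effect is a different problem from multiplicity.

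**Conclusion.** The point holds in this form: the article designates no deciding outcome, window or contrast, and the variable used for sizing has no defined 24 hours. Counted from sensor fitting, the first listed 24-hour period is about two-thirds pre-exercise (16.5/24 = 69%), and the most direct post-exercise day is not listed at all.

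If all 98 cells are tested, the expected cost lies between about 1.9 false high-versus-low differences (efforts equal, exercise different from control) and 4.9 false omnibus results (no condition different). The first figure assumes 15 completers and 28 error df. The chance of at least one false omnibus result depends on correlations that the article does not give, and is well below 99% if they are strong. This should be corrected; it does not invalidate the design.

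**What to change.** Before allocation is revealed, add one paragraph to the protocol or analysis plan that:
- designates average glucose in one defined post-exercise 24-hour window as primary, for example from session start, which the planned recording covers;
- names high minus low as the primary contrast;
- names one key psychological outcome;
- labels all other variables and windows secondary or exploratory, reported as estimates with 95% CIs.

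The window has to be presented as a new choice, because the article does not say the trial was sized on the 24 h after session start. If the registration record already names a primary outcome, the paragraph should agree with it or explain the difference.

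The cost is that the other metrics can no longer carry confirmatory significance claims. No extra data or participants are needed. Dropping area under the curve where it duplicates the mean is optional.

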### Data Monitoring Committee

A data and safety monitoring board will be composed of 2 medical doctors (a diabetes specialist clinician and a sports medicine specialist) and a biostatistician. The board will meet quarterly to address data and safety stemming from data collection. Specifically, they will analyze data related to adverse events related and unrelated to the study: musculoskeletal injuries (muscle strain, bruising, joint pain, back pain, etc), cardiovascular issues (increased blood pressure, arrhythmia, angina, myocardial infarction, etc), acute illnesses and symptoms (bronchitis, pneumonia, asthma attacks, flu, heart attacks, strep throat, respiratory infections sore throat, fever, cough, diarrhea, sneezing, headaches, etc), falls, syncope, aggravation of preexisting conditions (arthritis, tendinopathy, etc), hospitalizations, and death. The board will also analyze the dropout rate, as well as the reasons for dropping out. The board will make independent decisions and will have no conflict of interest regarding data collection, analysis, interpretation, and publication.

### Ethical Considerations

This study’s protocol and informed consent were submitted to and approved by the University of New Mexico IRB (protocol # 2310089095), and all procedures will follow the ethical standards of the IRB on human experimentation and the Helsinki Declaration of 1975, as revised in 2000. The study was prospectively registered in a public clinical trial registry [64]. Any modifications to the protocol will be submitted to the ethics committee, followed by an update of the trial registry. To promote participant retention, financial compensation (USD $200) for their time and effort will be provided.

For data sharing, all personal identifiers will be stripped from the data. Specifically, any direct identifiers (name, email addresses, phone, and cell phone numbers), date identifiers (birthday, date of disease diagnosis, and dates patients participated in data collection), location identifiers (personal or professional addresses and zip codes), links to external datasets identifiers (social media accounts) will be removed. Furthermore, participants will be represented by an ID string generated randomly, and their data will be inserted in the files in a random order, not associated with the order they were enrolled. Thus, data will be entirely deidentified before sharing, in order to protect sensitive personal information and privacy.

## Results

As of June 2024, we have performed pilot studies and recruited 2 potential participants. The anticipated data collection period will be from June 2024 to May 2025, and the final manuscript is expected to be submitted for publication by August 2025.

## Discussion

### Potential Impact and Significance of the Study

The results of this study will contribute to a better understanding of the effects of resistance exercise in individuals living with prediabetes and T2D and will be relevant to trainers and therapists who seek to incorporate resistance exercise in their client’s or patient’s routine. Specifically, understanding how short-term glycemic control is affected by altering resistance exercise prescription, in the case of this study, degree of effort, and assessing how this affects psychological responses bears clinical and practical relevance. We anticipate that glycemic control will be similarly improved independently of effort, but participants will experience more positive feelings after the low-effort session. As feelings experienced during a resistance exercise session may be predictive of long-term adherence, this would suggest that correct manipulation of the degree of effort during a resistance exercise session might confer better long-term outcomes for individuals living with prediabetes and T2D.

### Strengths and Weaknesses

This study will take advantage of the latest technology to track glycemic control using a CGM device and accelerometry to directly assess physical activity levels. These are much better approaches compared with other glycemic (handheld glucometers or the oral glucose tolerance test) and physical activity (self-reported questionnaires) assessments, which would increase the reliability of the data as well as its application to real-world scenarios. Also, strict dietary control will be used, and glucose-lowering medication will not be altered, in order to tease out the specific effects of resistance exercise on glycemic control. Finally, a blinded statistician not directly involved in data collection will analyze data, in order to minimize any bias and increase the significance of our findings.

In this study, we will try to anticipate participants’ performance in the high-effort trial by performing a fifth and final familiarization session. This is necessary in case the low-effort trial is randomized to happen before the high-effort one, as the number of repetitions during the low-effort session will be prescribed as half of the high-effort session. However, if the number of repetitions performed in the high-effort session is different from the fifth familiarization session, this could introduce error. Also, to increase the external validity and scope of our results, we will include both male and female participants within a wide age range, as there is evidence that sex and age affect glycemic control [65-74] and response to glucose-lowering drugs [75-79]. Finally, because it has been demonstrated that glycemic control is worsened during the luteal compared with the follicular phase in premenopausal women [80], menstrual cycle phase might be a confounding factor in the present protocol.

## Appendix

Multimedia Appendix 1

Multimedia Appendix 2

Multimedia Appendix 3 SPIRIT (Standard Protocol Items: Recommendations for Interventional Trial) 2013 checklist.

Multimedia Appendix 4 World Health Organization trial registration dataset.

Multimedia Appendix 5 Approved informed consent.

## Abbreviations

CGM: continuous glucose monitoring
CONSORT: Consolidated Standards of Reporting Trials
HbA1c: glycated hemoglobin
IRB: Institutional Review Board
RM: repetition maximum
SPIRIT: Standard Protocol Items: Recommendations for Interventional Trial
T2D: type 2 diabetes
TiDieR: Template for Intervention Description and Replication
